## Abstract

**Background:**

Cardiac auscultation remains an efficient and accessible diagnostic tool, especially in resource-limited countries where modern diagnostic devices like cardiac ultrasound are expensive and difficult to access. However, cardiac auscultation skills of medical students and physicians are declining, mainly because of an ineffective teaching method for this technique. The objective of this study is to evaluate the effect of a digitally enhanced cardiac auscultation learning method on participants’ theoretical knowledge and auscultation skills.

**Methods:**

This will be a controlled study with two parallel arms (1:1). Participants (fourth-year medical students) will be divided into two groups: an intervention group (receiving additional lectures, clinical internship and audio listening sessions) and a control group (receiving additional lectures and clinical internship). At the beginning of the study, all participants will undergo a pre-test that consist of two parts: a knowledge assessment based on multiple-choice questions and a skills assessment based on recognition of cardiac sounds from audio files. Thereafter, three specific additional lectures on cardiac auscultation will be delivered and all participants will take part in their official clinical internship. During these clinical internships (eight weeks), participants of the intervention group will be invited to two listening sessions based on five digital recordings of heart sounds. At the end of the clinical internship, all participants will be invited to a post-test to evaluate their knowledge, skills and satisfaction according to their learning method. The main outcome will be the participants’ knowledge progression. The other outcomes will be the participants’ skills progression, participants’ total progression and satisfaction. Data will be collected and analyzed in per protocol.

**Discussion:**

This study could contribute to the development of a learning method that takes into account the advantages of the conventional method and the contribution of digital technology. Positive results could lead to improved cardiac auscultation skills among health professionals, especially in developing countries.

**Supplementary Information:**

The online version contains supplementary material available at 10.1186/s12909-021-02807-4.

## Background

Auscultation is a technique used to diagnose diseases whose pathophysiological mechanisms involve the emission of characteristic sounds by the affected organs [1]. It is based on the use of the stethoscope, invented in 1816 by the French doctor René Laennec [1]. The development of auscultation has been a breakthrough in the diagnosis and management of heart and lung diseases, making it an integral part of clinical examination [2]. Despite the development of many modern diagnostic tools such as cardiac ultrasound, the mastery of auscultation remains a major challenge for health professionals given its effectiveness, efficiency and accessibility, particularly in countries with limited resources [3–6].

However, several studies have shown that the cardiac auscultation skills of medical students and physicians at all levels of training are declining [7–11]. This is explained not only by a decrease in interest in auscultation in favor of new diagnostic tools (echocardiography, MRI, etc.), but above all by an ineffective teaching method for this technique [12, 13].

Indeed, the conventional method of teaching clinical auscultation (lectures associated in a second time with clinical internships) has not evolved for nearly 50 years [12]. Classically, this teaching is done in two phases: (i) a theoretical phase in which the anatomical and physiological basis of the heart as well as the semiological characteristics of cardiac sounds are described and (ii) a practical (clinical) phase in which teachers listen to patients using a conventional stethoscope and identify characteristic sounds that they describe to learners who must then try to recognize the previously identified sounds.

This teaching and learning system may have some limitations, namely: the weak integration between the learning of theoretical knowledge and the acquisition of practical skills (knowledge is acquired long before it is put into practice); the lack of access to patients due to the large number of medical students and the variability of learning due to the diversity of patients and the variable evolution of the symptoms found in these patients [12, 14]. Digitalisation offers new perspectives to auscultation through functionalities like noise reduction, amplification and sound recording. Sound amplification and noise reduction improve sound perception, while recorded sounds can be replayed and shared with others. Consequently, several alternative methods of learning auscultation have been developed to modernize and strengthen this teaching in order to improve the skills of health professionals [12]. A hybrid learning method (conventional method reinforced by the use of digital) could improve the knowledge and skills of health professionals in auscultation and contribute to improve the quality of care, especially in resource-limited countries. The interest of this study is therefore based on the assessment of the relevance of this hybrid learning method and its effects on participants’ knowledge and skills.

## Objectives

### Primary objective

This study aims to evaluate effects of the use of a digitally enhanced auscultation learning method on participants’ cardiac auscultation performance.

### Secondary objectives

 The secondary objectives are to evaluate in both (intervention versus control) groups: (i) the progression of participants’ cardiac auscultation knowledge, (ii) the progression of participants’ cardiac auscultation skills (recognition of sound anomalies), (iii) the total progression of participants’ cardiac auscultation knowledge and skills and (iv) the participant satisfaction.

## Trial design

This will be a controlled study with two parallel arms in two centers (Fig. 1). Participants meeting the inclusion criteria will be divided into two groups (1:1): an intervention group (additional lectures associated with a clinical internship and listening sessions based on digital recordings of heart sounds) and a control group (additional lectures with a clinical internship). This study will take place over a six-month period, from the 1st September 2021 to the 1 March 2022 at the Faculty of Medicine and Biomedical Sciences of Yaoundé (FMBS) and at the Higher Institute of Medical Technologies (HIMT). The follow-up of participants from both groups and data collection will take place throughout the study.

**Fig. 1 Fig1:**
[figure not shown]
Design of the study

## Methods

### Study setting 

This study will take place in two centers: the Faculty of Medicine and Biomedical Sciences of the University of Yaoundé I (FMBS) and the Higher Institute of Medical Technologies (HIMT). These two institutions are medical training schools in Yaoundé, Cameroon.

### Eligibility criteria 

Eligible participants must be medical students newly admitted in to the fourth year of studies and willing to participate in this study. At this stage, they will have completed only nursing training courses.

Participants who did not participate to: (i) additional lectures, (ii) clinical internship, (iii) both listening sessions (based on digital recordings of heart sounds) for intervention group only, (iv) knowledge and skills assessments and (v) those who have withdrawn their consents will be excluded.

Repeaters students will not be included.

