### Assignment of interventions: allocation

#### Sequence generation

We have a potential risk of communication between participants in the intervention and control groups if they are in the same institution. To avoid this, participants in the control group will be selected only at HIMT while participants in the intervention group will be selected at FMBS. These two institutions are geographically distant and they organize their clinical internships in several hospitals at the same time.

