### Statistical methods

#### Statistical methods for primary and secondary outcomes

The use of statistical methods will be based essentially on the comparison of participants from the two groups according to defined outcomes. The average knowledge progression of participants in the intervention group will be compared against those in the control group using Student’s t-test if the variables follow the normal distribution or by a non-parametric test if not. The average skill progression and the average total progression in knowledge and skills (based on the total progression score) of the intervention group will be compared against those of the control group using a Student’s t-test if the variables follow the normal distribution or by a non-parametric test if not. The other continuous variables (the pre-test knowledge score, the pre-test skills score, the pre-test total score, the post-test knowledge score, the post-test skills score and the post-test total score.) will also be compared using parametric or non-parametric tests. The satisfaction of all participants (ordinal variable) will be analysed using a non-parametric test.

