### Methods for additional analyses (e.g. subgroup analyses)

No further analysis will be done.

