### Methods in analysis to handle protocol non-adherence and any statistical methods to handle missing data

Since the primary outcome measures the total progression of participants, it is necessary for each participant to go through the entire process. Participants with missing data will be excluded from the study.

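### The only stated analysis is per protocol, and its attendance rule has an extra hurdle in the intervention arm alone, which can bias the comparison by an amount the document cannot fix

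*Protocol article*

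**What the plan says.** The abstract of the protocol article fixes the analysis population: "Data will be collected and analyzed in per protocol". The section on eligibility criteria then lists exclusions that can only be known after enrolment. Some apply to both arms: "Participants who did not participate to: (i) additional lectures, (ii) clinical internship", followed by the knowledge and skills assessments and withdrawal of consent. One applies to a single arm: "both listening sessions (based on digital recordings of heart sounds) for intervention group only".

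The section on protocol non-adherence and missing data supports the same approach. It holds that "it is necessary for each participant to go through the entire process" and that "Participants with missing data will be excluded from the study". Under methods for additional analyses the protocol states "No further analysis will be done".

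The primary outcome, in the outcomes section and Table 1, is the post-test knowledge score minus the pre-test knowledge score. The two arms are compared "using Student’s t-test if the variables follow the normal distribution or by a non-parametric test if not", with no adjustment. Allocation is by school: "participants in the control group will be selected only at HIMT while participants in the intervention group will be selected at FMBS".

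**The concern.** Membership of the analysis set depends on behaviour after enrolment, and the behaviour required differs between arms. Lectures, internship and tests filter both arms. The listening sessions filter only the intervention arm, because controls have no comparable extra activity to miss.

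Students who turn up to sessions they are invited to may also be those who study harder. If so, the retained intervention group is more selected than the retained control group. Its mean progression would then be higher even if the sessions did nothing, and the unadjusted test would not correct for this.

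The rule also discards observed data: a student who sat both tests has a complete primary outcome whether or not the sessions were attended. The result describes full attenders, not students offered the method, and no stated analysis would show whether the exclusion mattered.

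**Working it through.** **1. Is the exclusion needed for the outcome?** The non-adherence section justifies it on the ground that the primary outcome is total progression. The outcomes section and Table 1 make the primary outcome knowledge progression and list total progression as secondary. Either one is a post-test score minus a pre-test score. Attendance enters neither, so two completed tests are enough.

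**2. Which hurdles are shared?**

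| Ground for exclusion | Intervention | Control |
|---|---|---|
| Additional lectures missed | yes | yes |
| Internship missed | yes | yes |
| Assessments missed | yes | yes |
| Consent withdrawn | yes | yes |
| Listening sessions missed | yes | no counterpart |

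Only the excess exclusion in the intervention arm produces the bias considered here.

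**3. The plan's own figures.** A two-sided comparison of 80% with 40% at 5% alpha and 80% power, without continuity correction, gives 23 per arm, or 46. Then 46 × 1.2 = 55.2, taken up to 56, or 28 per arm. Both stated figures reproduce. The 20% covers refusal, absenteeism and loss to follow-up in both arms together. It is not a forecast of listening-session absence.

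**4. Illustration under no true effect.**

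*Inputs.* From the protocol: 28 per arm. Assumed, because the document gives no value:
- 20% of the intervention arm excluded (28 × 0.8 = 22.4, so 22 kept);
- correlation ρ of 0.3 to 0.5 between attendance propensity and progression;
- 28, 25 or 24 controls kept.

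*Formula.* If a fraction f with the lowest propensity is removed, the mean progression of those who remain rises by ρ × λ(f) SD, where λ(f) = φ(z_f)/(1 − f). The bias is ρ × [λ(f in intervention) − λ(f in control)].

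- λ(6/28) = 0.2916/0.7857 = 0.371
- λ(3/28) = 0.1845/0.8929 = 0.207
- λ(4/28) = 0.2256/0.8571 = 0.263

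*Results.* The formula is a large-sample approximation. The last two columns come from 40,000 simulated trials per row, with a t-test on the students kept.

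| Controls kept | ρ | Formula bias (SD) | Simulated bias (SD) | Two-sided type I error |
|---|---|---|---|---|
| 28 | 0.3 | 0.3 × 0.371 = 0.111 | 0.107 | about 6.8% |
| 28 | 0.5 | 0.5 × 0.371 = 0.186 | 0.179 | about 10% |
| 25 | 0.3 | 0.3 × (0.371 − 0.207) = 0.049 | 0.047 | about 5.5% |
| 25 | 0.5 | 0.5 × (0.371 − 0.207) = 0.082 | 0.080 | about 6.6% |
| 24 | 0.3 | 0.3 × (0.371 − 0.263) = 0.032 | 0.034 | about 5.5% |
| 24 | 0.5 | 0.5 × (0.371 − 0.263) = 0.054 | 0.050 | about 6.1% |

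Repeated runs differ by a few tenths of a percentage point. Across runs the range is about 5.3 to 6.7% with 24 or 25 controls kept, and about 7 to 10% with all 28 kept.

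**5. Size against the design.** As a comparison of means, 23 per arm at 80% power corresponds to (1.96 + 0.84) × √(2/23) = 0.83 SD. A bias of 0.03 to 0.08 SD is 4 to 10% of that (0.03/0.83 to 0.08/0.83). A bias of 0.18 SD is 22%.

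**The case against.** Several points on the other side stand.

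- **Controls are filtered too.** A reader might infer that every equally disengaged control stays in. The text does not support that: controls who miss lectures, internship or a test are removed as well. The rows with all 28 controls kept are therefore an upper scenario, not an estimate.
- **Direction and size are assumed.** That the rule must favour the intervention is another tempting inference. The document gives no link between attendance and progression. The outcome is a change score, so stable ability partly cancels. Stronger students may also start higher on a 15-item test and have less room to gain.
- **The wording is open.** Not taking part in both sessions may mean missing either one or missing the two. The requirement to complete the whole process points to the stricter reading but does not settle it. On the looser reading fewer students are lost, but the hurdle is still in one arm only.
- **The arms are not randomised.** Analysis as assigned cannot preserve a randomised comparison that was never made. Confounding by school remains whatever is done here.
- **Per protocol is declared openly, and attendance is supported** by calls, SMS and scheduling around classes. The effect among students who completed the training is a legitimate, narrower question. The statement that no further analysis will be done stands under a heading that gives subgroup analyses as its example, so it is not an explicit ban on another analysis population.

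These points reduce the size and certainty of the concern. None supplies a matching hurdle for controls, and none explains why students with both test scores should be dropped.

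**Conclusion.** The concern holds in a limited form. The protocol sets an attendance hurdle in one arm only, makes per protocol the only stated analysis, and so can discard complete primary outcomes from intervention students alone. The likely direction is in favour of the intervention, provided that attendance reflects motivation.

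Under the assumptions above, the bias is 0.03 to 0.08 SD when controls also lose 3 or 4 of 28 students, and 0.11 to 0.18 SD when they lose none. Neither the correlation nor the exclusion rates come from the document, so these figures illustrate and do not estimate. A bias of this size is unlikely on its own to reverse the conclusion if the planned difference is real. It matters more if the true effect on knowledge is small. It also adds to the confounding by school. The plan should be changed, but this point alone does not invalidate the study.

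**What to change.** Make the primary analysis all enrolled, consenting students with a pre-test, in their assigned group, whatever their attendance at lectures, internship or listening sessions. Attendance criteria (i), (ii) and (iii) should then no longer define the primary analysis set. Deleting only (iii) would leave selection on attendance after enrolment in place.

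Invite every student to the post-test, including those who missed sessions, through the calls and SMS already planned. Keep the per-protocol set as a labelled sensitivity analysis, and state whether missing one listening session or only missing the two removes a student from it.

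If post-tests are missing, replace exclusion by a likelihood-based or multiple-imputation analysis using pre-test score and arm. School is the same variable as arm and adds nothing to the model. Amend the abstract and the non-adherence section to match.

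The cost is a change of wording and the effort of following absentees to the post-test. The estimated effect may be somewhat smaller. No new sample-size figure is needed for this change. It should be settled before data collection, because a post-test not taken at the time cannot be recovered. It does not remove the confounding by school.

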### Informed consent 

 Informed consent will be obtained from each participant. This will be done during an interview in which an information sheet and an informed consent form will be explained and given to them.

### Additional consent provisions for collection and use of participant data and biological specimens

Not applicable.

### Interventions

### Explanation for the choice of comparators

The conventional method (lectures and clinical internship) will be chosen as the comparator because it is the most used learning method of cardiac auscultation. This method consists in learning of cardiovascular and respiratory semiology in the third year and in learning of clinical pathology and clinical internships in the fourth year of medical studies respectively.

### Intervention description : intervention group

Three main activities will be organized: additional lectures, clinical internship and listening sessions based on digital recordings of heart sounds.

#### Additional lectures

Three additional lectures will be prepared by research team in agreement with a scientific committee composed of cardiologists. These lectures aim at supporting the normal lectures delivered in these faculties. The first course will focus on the anatomical and physiological bases of the heart, the second on cardiac semiology and the third on cardiac auscultation. These courses will take place at the FMBS and will be delivered in two sessions: the first course (first session) will take place on the same day as the recruitment of participants, the second and third course (second session) will take place two or three days after the first. Each course will be administered using PowerPoint presentation software and will have a duration of one hour (30 min of teaching and 30 min of question-and-answer session). These courses are complementary to other theoretical lectures in clinical semiology which are delivered in the amphitheater or in the clinical departments in which they have an internship and which correspond to the training program of 4th year of medical studies.

#### Clinical internship

Participants in the intervention group will be required to participate in their official clinical internship (internal medicine) as planned by their training school. This internship will take place in all the hospitals in Yaoundé that are accredited by the FMBS, namely the Central Hospital, the General Hospital, the University Hospital Centre and the Jamot Hospital. It will start after the delivery of additional lectures, over a period of two months. The objective is to introduce participants in a practical way to the patient’s cardiac examination (inspection, palpation, percussion and auscultation) and to reinforce their knowledge of cardiac semiology. These objectives will be achieved through activities such as medical observations, daily follow-up of hospitalized patients, practical cardiac semiology sessions and participation in scientific symposia. These activities are most often done under the supervision of a teacher or of an academic elder, a resident or an intern.

#### Listening sessions based on digital recordings of heart sounds

##### Preparation of the material

Five (5) digital audio recordings from real patients will be selected from a cardiac auscultation database designed in Cameroon in 2017 [15]. These recordings were made using a Littmann© 3200 electronic stethoscope and the resulting audio files were annotated using Audacity © software under the supervision of a cardiologist and then stored on a computer in WAV format.

Each recording corresponds to a specific cardiac sound and lasts for one (1) minute; the target cardiac sounds are as follows: heart sounds B1 and B2, aortic stenosis murmur, third heart sound (B3), fine crackles of heart failure and atrial fibrillation murmur. The selected recordings will be stored on a computer.

##### Listening sessions

Two listening sessions of these digital recordings will be held in an FMBS classroom. Each session will be held for one hour. Each session will be organized in 3 parts: 10 min for the introduction of the activity and the presentation of tools; 40 min for listening during which each participant will have access to the 5 selected digital audio recordings of heart sounds and 10 min for feedback (collection of participants’ opinions and impressions). These recordings will be played back in a loop (series of 5) to the participants using a computer connected to loudspeakers and the Audacity© software. Four series of 10 min will be made. During these series, each recording will be broadcast for 2 min, for a total of 10 min per serie. The first series will be commented by the supervisor to help participants to identify auscultatory anomalies.

A multimedia package containing the additional lectures and the 5 digital audio recordings will be designed and made available to each participant in the intervention group at the end of the second listening session. Participants will be recommended to use this support to independently conduct similar listening sessions as often as they wish. SMS reminders will be sent to participants to encourage them to use this support.

